# Introduction and Study Rationale

Health as well as the development and course of diseases are determined by very different factors. Many of those factors are particularly influenced by the professional environment. On the one hand, in a positive sense, e.g., by way of experiencing recognition, being creative and productive or establishing social contacts, which can help to cope with stressful situations. On the other hand, in a negative sense, e.g., in cases where the modern, compact world of work is very demanding and, thus, creates feelings of excess strain or isolation. Due to cost-cutting measures, working areas in hospitals and clinics have been subject to enormous changes over the last few years, especially with regard to the working conditions.

Hospital employees are a particularly vulnerable group because of their high occupational stress levels (Dollard et al., 2007). In a systematic review (Dollard et al., 2007), the individual and organisational impact of work-related stress in the Australian and international health and social services (HCS) sectors were examined. The results demonstrate high levels of occupational stress in the HCS sector. Work stress had a negative impact both on the individual (e.g. mental health) and on the organisation (e.g. absenteeism, job dissatisfaction).

Although health care workers show increased work-related stress and suicide rates (Agerbo et al., 2007), most of the hospitals in Germany lack of a systematic occupational health management system which links behavioural and organizational prevention. The high complexity of the hospital is often cited as a reason for this lack. As a reaction, often only occupational health promotion takes place in "campaignable" sub-areas or individual occupational groups (van Wyk & Pillay-Van Wyk, 2010). The evidence of individual intervention types has only been partially proven. In particular, the evaluation of combined behavioral and organizational interventions in the health care system is still outstanding (Ruotsalainen et al., 2015). In other sectors, some studies indicate an increased effectiveness of the combination of these two intervention types (Tetrick & Winslow, 2015). Existing reviews emphasize the need for methodologically high-quality studies in the field of health promotion in hospitals (Ruotsalainen et al., 2015; van Wyk & Pillay-Van Wyk, 2010).

The construct psychosocial safety climate (PSC) refers to policies, practices, and procedures that aim to protect workers psychological health and safety. According to Dollard and Bakker (2010), PSC is a facet-specific element of organizational climate, a ‘climate for psychosocial health and safety’, which is expected to precede working conditions.

A related construct represents the safety climate construct (Zohar, 2010).This construct focuses on policies and practices regarding safety and protection from physical hazards in the workplace, whereas psychological health and safety at work receive far less attention. The extension of the construct to psychological health seems important from a health and social policy perspective, as it can improve strategies and procedures to protect the mental health of employees (Dollard, 2012).

One of the major challenges in work stress research is to identify the origin of work stress so that interventions can be used as efficiently and effectively as possible. Existing research is characterized by work stress theories that focus on the conditions of job tasks as the origin of work stress. However, since companies are complex multi-layered systems (Mathieu & Taylor, 2007), the origin of work stress could lie in the dynamic interaction of different levels of influence (e.g. the organization, and/or individual). The PSC theory allows a multi-level perspective on work stress (Dollard, Opie et al., 2012).

The purpose of this study is to examine whether a complex intervention consisting of combined behavioral and organizational interventions for different target groups in hospital can reduce the work-related stressors of hospital staff and contribute to the improvement of their mental health and well-being.

# Trial Objectives and Purpose

This trial will evaluate the effect of a complex intervention on mental health and well-being of employees working in hospital.

## Primary objective

It will be assessed whether a complex intervention consisting of behavioural and structural preventive elements leads to an improvement in subjectively perceived emotional and cognitive strain of hospital employees measured with the irritation scale compared to standard care.

## Secondary objectives

The trial will also evaluate the effect of the complex intervention on the perceived emotional and cognitive strain in the working environment, subjective psychological well-being, the improved psychosocial safety climate, the perceived occupational effort as well as the perceived occupational rewards, the perceptions of working conditions, leadership and communication style and organizational indicators on individual/participant level as well as on hospital/clinic level. In this context, cluster participants not partaking in the modules will also be asked about their perception in order to evaluate a possible influence of the complex intervention on the organisation level.

## Process evaluation

Furthermore, a thorough process evaluation will be part of this trial. Up to four expert interviews will be conducted with persons not involved in the study to prepare the development of the interviews guidelines. In line with the best available evidence (Moore et al., 2015), a mixed-methods approach will be used. First, focus groups (Richter et al., 1991) (about N = 8 per group) will be conducted with a subsample of participants from all study sites before and after the implementation of the intervention to identify participants’ attitudes, perceptions, and experiences regarding the intervention. Three pre-post focus groups will be held at each study site, with participants representing an adequate mix of targets groups. If new and interesting topics relevant for the process evaluation are coming up during the interviews, additional interviews via video conferences will be conducted with participants from different study sites. The interviews will be analysed using qualitative content analysis (Mayring, 2015) via MAXQDA after transcription. Second, the entire aggregated data set will be subjected to comprehensive multivariate analysis using multilevel modelling to identify mediators and moderators of effect with a focus on context (e.g. organizational indicators), intervention (e.g. fidelity), participant characteristics, process measures (e.g. self-efficacy), and satisfaction ratings. Process evaluation includes the development of a pragmatic SEEGEN fidelity scale. The fidelity scale aims to assess and monitor fidelity of the complex process of intervention implementation in SEEGEN. Development of the scale and item selection was guided by recommendations of relevant methodological literature (Breitenstein et al., 2010; Carroll et al., 2007; Feely et al., 2018; Ibrahim & Sidani, 2015). Operational fidelity as the degree to which the intervention is delivered according to the original plan was a leading feature. A consensus-based selection of the final items was performed with a systematic rating within the study group. Five specific dimensions of fidelity are addressed:

1. Exposition (dose, frequency and duration of contact to the intervention)
2. Engagement (extent to which the participants are involved in the intervention activities and capture activities during the intervention sessions)
3. Enactment/adherence (extent to which participants actively apply the skills learned during the intervention in their daily routine)
4. Perceived competence and skills of the interventionist
5. Satisfaction with the intervention

The SEEGEN fidelity will be administered to recipients of the intervention alongside the SEEGEN RCT.

# Outcomes

## Primary Outcome

The outcome will be the change in the total score of the IRR (Mohr et al., 2005) from baseline (T0) to 11 months after baseline (T2*). The eight-item IRR assesses the emotional and cognitive strain in the working environment. Items are measured on a 7-point Likert scale, ranging from 1 (not at all) to 7 (almost completely correct).

## Secondary Outcomes

### Main secondary outcomes

- Change in the World-Health Organization Well-Being Index (WHO-5) from T0 to T2*. The WHO-5 is described below.
- Change in Psychosocial Safety Climate (PSC-12) from T0 to T2*. The PSC-12 is described below.

### Further secondary outcomes

In addition to the primary outcome, the change in the total score of the IRR from baseline to 11 months after baseline (T1*) will be evaluated as well as the changes from T0 to T1* and from T0 to T2* for both subscales, respectively. Further secondary outcomes are the change from T0 to T2* and from T0 to T1* in:

- World Health Organization Well-Being Index (WHO-5 Well-Being Index, Topp et al., 2015)

Subjective psychological well-being will be measured using the five-item World Health Organization Well-Being Index (WHO-5). Items are measured on a 6-point Likert scale, ranging from 0 (at no time) to 5 (all of the time). The raw score ranging from 0 to 25 is multiplied by 4 to give the final score ranging from 0 representing the worst well-being to 100 representing the best well-being.

- Psychosocial Safety Climate (PSC-12)

Psychosocial safety climate will be measured using the 12-item Psychosocial Safety Climate Scale (G. B. Hall et al., 2010). The PSC-12 consists of four dimensions: (1) organization participation (3 items), (2) organization communication (3 items), (3) management priority (3 items) and (4) management commitment (3 items). Items are measured on a 5-point Likert scale, ranging from 1 (strongly disagree) to 5 (strongly agree).

- Effort-Reward Imbalance Scale – Short version (ERI; Siegrist et al., 2009).

Effort will be measured by three items (ERI1-ERI3). Items are measured on a 4-point Likert scale, ranging from 1 (strongly disagree) to 4 (strongly agree) with higher sum score between 3 and 12 indicating more perceived efforts. Reward is measured by seven items (ERI4-ERI10). A low sum score of these items between 7 and 28 represents fewer perceived occupational rewards.

- Work Analysis Instrument for Hospitals – Self-Report Version (Tätigkeits- und Arbeitsanalyseverfahren für das Krankenhaus; TAA-KH-S; Glaser, 1997)

Two scales of a German questionnaire for hospital employees will be used to measure their working conditions: (1) scope of action (shortened from 9 to 3 items); (2) temporal overload (3 items). Items are measured on a 5-point Likert scale, ranging from 1 (no, not at all) to 5 (yes, absolutely).

- Questionnaire on integrative leadership (FIF) (Rowold & Poethke, 2017)

The questionnaire on integrative leadership is a standardized instrument which records leadership and communication style in four modules (module A: transformational and transactional leadership, module B: instrumental leadership, module C: communication and module D: negative leadership). In this study, module A in its self-assessment for leaders and its external assessment for subordinates will be used. The multidimensional construct of transformational leadership consists of six core behaviors (“fostering innovation”, “team spirit development”, “performance development”, “individuality focus”, “providing a vision” and “being a role model”). Participants have to rate 24 statements at a five point Likert-scale from 1 “agree not at all” to 5 “totally agree”. The items` ratings can be summarized to 10 different scale scores or to one overall score each (transformational leadership, transactional leadership and negative leadership). The scales of transformational leadership show a sufficient intern consistency with Cronbach`s α = .79 – .92 for the external assessment and Cronbach`s α = .71 – .83 for the self-assessment (Rowold & Poethke, 2017).

- Short version of the Occupational Self-Efficacy Scale (SOSES; Rigotti et al., 2008)

Occupational self-efficacy will be measured using the Short version of the Occupational Self-Efficacy Scale. The instrument consists of 6 items rated on a six-point Likert scale ranging from 1 (not at all true) to 6 (completely true) with higher values reflecting higher occupational self-efficacy.

- Top Management Evaluation Sheet

Participants in the top management will be asked to complete an evaluation form consisting of 29 items. The questions relate to measures to promote the mental health of employees at the hospital (e.g. offers for stress prevention, activities to improve working conditions) and the role of the management in this issue.

- Organizational indicators on individual/participant level:
  1. Job satisfaction (Fischer & Lück, 2001; 8 items, measured on different 5-point Likert scales, ranging from 1 “wrong” to 5 “right”, 1 “not at all interesting” to 5 “yes, very interesting”, 1 “very view opportunities” to 5 “yes, a lot of opportunities”, 1 “very discontent” to 5 “yes, very content”, 1 “definitely not” to 5 “yes, for sure”)
  2. Employer attractiveness (Bruhn et al., 2013; 5 items, measured on a 7-point Likert scale, ranging from 1 “strongly disagree” to 7 “strongly agree”)
  3. Presenteeism (Preisendörfer, 2010; 1 item, measured on a 5-point scale; “never”, “seldom”, “occasionally”, “frequently”, “very often”)
  4. Intention to leave (Simon et al., 2005; 1 item, measured on a 5-point scale; “never”, “a few times a year”, “a few times a month”, “a few times a week”, “everyday”)
  5. Absenteeism (modified version of Caverley et al., 2007; 1 item, “Please estimate, how many days on average per month you are being absent due to an illness.”)
  6. Recommendation (modified version of Reichheld, 2003; 1 item, measured on an 11-point Likert scale, ranging from 1 “highly unlikely” to 11 “highly likely”)
  7. Work overtime (“How many hours have you worked overtime in the past month?”; “What is your contracted duration of working time per week (in hours)?”)
  8. Economic situation of clinic/unit (adapted version of A. Hall & Rohrbach-Schmidt, 2013, “How do you assess the economic situation of the clinic/unit you work at?”, measured on a 5-point Likert scale, ranging from 1 “very good” to 5 “don’t know”).
  9. Job security (Lee et al., 2004, “My job security is good”, measured on a 4-point Likert scale, ranging from 1 “strongly disagree” to 4 “strongly agree”).
  10. Cooperation between occupational groups (Glaser, 1997, shortened from 5 to 2 items, TAA-KH-S subscale social climate, measured on a 5-point Likert scale, ranging from 1 “no, not at all” to 5 “yes, absolutely”).
- Exposure and (mental) effects caused by COVID-19 (12 items and five open questions for example on the extend of (mental) burden, actions by the employer and coping with the pandemic)

Additional secondary outcomes will be colltected at T2 only:

- Personal data that provide information about the number of own children, childcare facilities and the partner's work activity (9 items),
- Trierer Scale to measure Work-Life Balance (TKS-WLB, Syrek et al., 2011)

Work-Life Balance will be measured using the Trierer Scale to measure Work-Life Balance. The instrument consists of 5 items rated on a six-point Likert scale ranging from 1 (strongly disagree) to 6 (strongly agree).

- Copenhagen Psychosocial Questionnaire

The subscales “emotional demands” and “hiding emotions” of the Copenhagen Psychosocial Questionaaire will be used to measure emotional demands at work (COPSOQ , 4 items Nübling, 2005). Items are measured on a 5-point Likert scale, ranging from 1 (to a very large extent) to 5 (to a very small extent).

Moreover, some organizational indicators on hospital/clinic level will be collected annually via request from the hospitals accounting division and will be assigned to the clusters, if possible, depending on the level of detail of the data and the homogeneity/heterogeneity of the clusters.

- 1. Turnover ($\text{turnover rate = }\frac{\text{number of employees who left in year x}}{\text{total number of employees at the beginning of year x}}\text{ x 100}$,

number of applicants, number of persons hired, number of persons retired, number of dismissals, number of expiring fixed-term contracts)

- 1. $\text{Absence rate = }\frac{\text{absence (in hours) in year x}}{\text{gross working time (number of employees * working hours per week) in year x}}\text{ x 100}$
  2. Work overtime rate = $\frac{\text{work overtime (in hours) in year x}}{\text{contracted working time }\text{(}\text{in hours}\text{)}\text{ in year x}}\text{ x 100}$
  3. $\text{Sickness} \text{absence rate = }\frac{\text{sickness absence }\text{(}\text{in hours}\text{)}\text{ in year x}}{\text{planned working time }\text{(}\text{in hours}\text{)}\text{ in year x}}\text{ x 100}$
  4. Age distribution = number of employees sorted by age classes

In addition, participants of a cluster who decide not to participate in the modules (cluster participants) will be asked to complete a shorter questionnaire at T0, T1* and T2* consisting of the following measurements:

- - - IRR (Mohr et al., 2005), as described above,
    - WHO-5 (Topp et al., 2015), as described above and
    - PSC-12 (G. B. Hall et al., 2010), as described above,
    - GTL (Carless et al., 2000) scale to measure transformational leadership and
    - COVID-19 measures, as describes above.

Based on single items, they will be asked about their perception of the needs and benefits (personal and for the units they work at) of the module-offer, too. The outcome will be the change in the scores of IRR, WHO-5, PSC-12, GTL and single items from T0 to T2*, as well as from T0 to T1*.

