**Further secondary outcomes:**

- Change in the total score of the IRR from T0 to 6 months after baseline (T1*) as well as the changes from T0 to T2* and T0 to T1* for both subscales between the intervention and waitlist control group.

The change in scores from T0 to T2*, as well as from T0 to T1*, between the intervention and waitlist control group of the following:

- World Health Organization Well-Being Index (WHO-5 Well-Being Index, Topp et al., 2015)
- Psychosocial safety climate (PSC-12; 12 items, G. B. Hall et al., 2010)
- Effort-Reward Imbalance Scale – Short version (ERI, 10 items, Siegrist et al., 2009)
- Work Analysis Instrument for Hospitals – Self-Report Version (2 subscales, 6 items, Glaser, 1997)
- Questionnaire on integrative leadership (FIF, 24 items) (Rowold & Poethke, 2017)
- Short version of the Occupational Self-Efficacy Scale (SOSES; 6 items, Rigotti et al., 2008)
- Top Management Evaluation Sheet (only for top management*)*
- Organizational indicators on individual/participant level (Job satisfaction, 8 items, Fischer & Lück, 2001; Employer attractiveness, 5 items, Bruhn et al., 2013, Presenteeism, 1 item, Preisendörfer, 2010; Intention to leave, 1 item, Simon et al., 2005; Recommendation, 1 item, modified version of Reichheld, 2003; Absenteeism; 1 item, modified version of Caverley et al., 2007; Work overtime; Economic situation of clinic/unit; 1 item, adapted version of A. Hall & Rohrbach-Schmidt, 2013; Job security; 1 item, Lee et al., 2004; Cooperation between occupational groups, 2 items, TAA-KH-S subscale social climate, Glaser, 1997)
- Organizational indicators on hospital/clinic level (Turnover rate, Number of applicants, Number of persons hired, Number of persons retired, Number of dismissals, Number of expiring fixed-term contracts, Absence rate, Work overtime rate, Sickness absence rate, Age distribution) requested from the participating hospitals’ accounting divisions

The change in scores from T1* to T2*, between the intervention and waitlist control group of the following:

- COVID-19 exposure and (mental) effects (concerns about COVID-19, trust in employer etc.; 12 items, five additional open questions)

The change in scores from T0 to T2*, as well as from T0 to T1*, between cluster participants (no module participation) of the following:

- IRR (Mohr et al., 2005)
- WHO-5 Well-Being Index (Topp et al., 2015)
- PSC-12 (G. B. Hall et al., 2010)
- Global Transformational Leadership (GTL; Carless et al., 2000)

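### Three definitions of exploratory organisational outcomes are wrong as printed: annual data for a six-month change, a weekly denominator under a yearly numerator, and a non-answer as a scale point

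*Protocol*

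**What the plan says.** **Timing of the hospital/clinic-level indicators.** Section 6.2.2 states that "some organizational indicators on hospital/clinic level will be collected annually via request from the hospitals accounting division", and its rate formulas refer to a year x. The Protocol Summary opens its list of further secondary outcomes with "The change in scores from T0 to T2*, as well as from T0 to T1*, between the intervention and waitlist control group of the following", and that list includes "Organizational indicators on hospital/clinic level (Turnover rate, Number of applicants, Number of persons hired" and the remaining rates. Table 1 marks turnover, absence rate, overtime rate, sickness absence rate and age distribution at T0, at T1* (6 months, plus or minus 1) and at T2* (11 months, plus or minus 1). The Summary dates recruitment from 10/2019 to 03/2020.

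**Absence rate.** The numerator is "absence (in hours) in year x". The denominator is "gross working time (number of employees * working hours per week) in year x". The overtime and sickness-absence rates next to it have hours in year x both above and below the line.

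**Economic situation of the clinic/unit.** Section 6.2.2 describes this single item as "measured on a 5-point Likert scale, ranging from 1 “very good” to 5 “don’t know". The Protocol Summary lists it among the individual-level indicators to be compared as changes in scores.

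**Status.** Section 13.2 confines confirmatory testing to the IRR, then the WHO-5, then the PSC-12. Everything else is exploratory and descriptive.

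**The concern.** These are declared secondary outcomes. Section 5.2 makes the organisational indicators an objective, and Section 5.3 names them as an example of context in the mediator and moderator models.

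The timing conflict is the most serious of the three. A statistical analysis plan can choose how to analyse data but cannot create a six-month value from a yearly one. The accounting divisions must be asked for finer data, or the contrast must go.

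The other two are defects in definitions that the protocol itself fixes. Different locations could apply the absence-rate bracket differently. A *don't know* answer is not a position between good and bad, yet it occupies the end opposite *very good* on a scale meant for change scores.

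**Working it through.** The protocol gives no numerical result for these outcomes, so there is no figure of its own to reproduce.

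**1. Annual data against T0, T1* and T2*.** Inputs: recruitment dates (Protocol Summary) and visit timing (Table 1). Assumption: year x is a calendar year.

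| T0 | T1* (T0 + 6 months) | T2* (T0 + 11 months) | Annual value used at T0 / T1* / T2* |
|---|---|---|---|
| Oct 2019 | Apr 2020 | Sep 2020 | 2019 / 2020 / 2020 |
| Nov 2019 | May 2020 | Oct 2020 | 2019 / 2020 / 2020 |
| Dec 2019 | Jun 2020 | Nov 2020 | 2019 / 2020 / 2020 |
| Jan 2020 | Jul 2020 | Dec 2020 | 2020 / 2020 / 2020 |
| Mar 2020 | Sep 2020 | Feb 2021 | 2020 / 2020 / 2021 |

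- T0 in 2019: T1* and T2* share the 2020 value, so the two changes are identical. That value also covers months after T1*.
- T0 from January to March 2020: T0 and T1* share the 2020 value, so the T0 to T1* change is zero by construction.
- T0 in March 2020: T2* would need the 2021 value. The Summary plans database lock for 06/2021, before that year is complete. Waitlist modules run after the intervention phase and end in 04/2021 (Section 10 and Summary), so the 2021 value may also include months with treated controls.

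The conclusion does not depend on the calendar-year assumption. T0 to T2* spans 11 months, at most 12 with the visit window, so three time points fall in at most two yearly periods, whenever the year begins. At least two of the three must share a value.

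**2. Absence rate.** Let A be absence hours in the year, N employees, h weekly hours and w weeks per year.

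- Literal: 100 × A / (N × h)
- Annual: 100 × A / (N × h × w)
- Ratio: w, whatever N and h are.

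The protocol does not give w; I assume 44 to 52.

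| True absence | Literal, w = 44 | Literal, w = 52 | Annual |
|---|---|---|---|
| 5% | 220% | 260% | 5.0% |
| 10% | 440% | 520% | 10.0% |

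Illustration (all inputs assumed): 40 employees, 38.5 hours per week, 15 absence days of 7.7 hours each, w = 52.

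- A = 40 × 15 × 7.7 = 4,620 hours
- Literal: 4,620 / (40 × 38.5) = 4,620 / 1,540 = 300%
- Annual: 4,620 / (1,540 × 52) = 4,620 / 80,080 = 5.8%

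The literal rate passes 100% once true absence exceeds 1/w, that is 1/52 = 1.9% to 1/44 = 2.3%.

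**3. Don't know coded 5.** If a share p answers *don't know* and the other answers average m, the item mean moves by p × (5 − m). Neither p nor m is in the protocol; I assume p from 5% to 20% and m from 2 to 3.

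- Smallest: 0.05 × (5 − 3) = 0.10
- Middle: 0.10 × (5 − 2) = 0.30
- Largest: 0.20 × (5 − 2) = 0.60

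These are shifts in one group's mean. For the contrast between arms, what counts is the difference in how the *don't know* share changes. A difference of 10 percentage points at m = 2 gives 0.30; equal movement in both arms largely cancels.

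**The case against.** **On the absence rate.** A reader might infer that the trial will report impossible rates, or that the outcome is meaningless. The document does not support that. The denominator is labelled gross working time in year x, the neighbouring formulas are coherent, and the natural reading is an annual total with the weeks factor left out of the bracket. Only one of the four rate formulas is affected. Even on the literal reading, a common factor rescales a comparison between arms without reversing it. Nor would the correction put the absence and sickness-absence rates on one base, since one uses gross and the other planned working time. What stands is a unit error in the only operational definition given. If some locations apply the weeks factor and others do not, it no longer cancels.

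**On the response scale.** A reader might infer that *don't know* is scored as the worst rating. The protocol never says so; that follows only from the code's position. Handling of such codes may be in the statistical analysis plan, which is not at hand. What stands is that the protocol itself calls this a 5-point Likert scale and lists it for change scores without qualification.

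**On timing.** Section 6.2.2 already hedges: assignment to clusters depends on the detail and homogeneity of the data. That concerns mapping to clusters, not frequency, and does not remove the conflict.

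**On importance.** All these outcomes lie outside the confirmatory hierarchy. This limits the weight of the point and stands in full.

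**Conclusion.** All three definitions are wrong as printed.

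1. **Timing: a direct contradiction** between Section 6.2.2 on one side and the Protocol Summary and Table 1 on the other. Annual values cannot yield a T0 to T1* change, and for T0 in late 2019 they cannot separate T1* from T2*. This holds whenever the year begins.
2. **Absence rate: a unit error in the wording.** Read literally, it inflates the rate by the number of weeks used, about 44 to 52 (assumed). An annual total was probably intended, so this does not show that wrong rates will be reported.
3. **Economic situation: a scale-definition error.** If scored as printed, the item mean moves by 0.10 to 0.60 points under the assumed shares and means. The effect on the contrast between arms is smaller unless *don't know* answers change differently by arm.

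The corrections are worth making because they are cheap and the first needs a different data request. The primary endpoint, the hierarchical tests and the sample size are untouched.

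**What to change.** **Timing.** Request monthly or quarterly figures where the accounting divisions can supply them, and align them to T0, T1* and T2*. Where they cannot, remove the T0 to T1* and T0 to T2* change claims from the Protocol Summary and Section 6.2.2, and the T1* and T2* marks from Table 1, for these indicators. Then report annual values for 2019 and 2020 by randomised arm, descriptively and only where the data map to clusters. State that these years only approximate the time before and after T0: with T0 in October 2019, the last months of 2019 already follow baseline; with T0 in March 2020, the first months of 2020 precede it.

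**Absence rate.** Define gross working time as employees × contracted weekly hours × weeks in year x, with one stated number of weeks used identically at all sites.

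**Economic situation.** Analyse codes 1 to 4 only, set *don't know* to missing, and tabulate it separately by arm. Print the labels of codes 2 to 4, which the protocol does not give, to confirm that they are substantive ratings.

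**Cost.** Wording changes in Section 6.2.2, the Protocol Summary and Table 1, plus a revised data request to the hospitals. No new participants or questionnaires are needed.
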